# Effectiveness of app-based relaxation for patients with chronic low back pain (Relaxback) and chronic neck pain (Relaxneck): study protocol for two randomized pragmatic trials

**DOI:** 10.1186/1745-6215-15-490

**Published:** 2014-12-15

**Keywords:** Neck pain, Low back pain, Relaxation, Mind-body therapies, Smartphone application, Comparative effectiveness research

## Abstract

**Background:**

Chronic low back pain (LBP) and neck pain (NP) are highly prevalent conditions resulting in high economic costs. Treatment guidelines recommend relaxation techniques, such as progressive muscle relaxation, as adjuvant therapies. Self-care interventions could have the potential to reduce costs in the health care system, but their effectiveness, especially in a usual care setting, is unclear. The aim of these two pragmatic randomized studies is to evaluate whether an additional app-delivered relaxation is more effective in the reduction of chronic LBP or NP than usual care alone.

**Methods/design:**

Each pragmatic randomized two-armed study aims to include a total of 220 patients aged 18 to 65 years with chronic (>12 weeks) LBP or NP and an average pain intensity of ≥ 4 on a numeric rating scale (NRS) in the 7 days before recruitment. The participants will be randomized into an intervention and a usual care group. The intervention group will be instructed to practice one of these 3 relaxation techniques on at least 5 days/week for 15 minutes/day over a period of 6 months starting on the day of randomization: autogenic training, mindfulness meditation, or guided imagery. Instructions and exercises will be provided using a smartphone app, baseline information will be collected using paper and pencil. Follow-up information (daily, weekly, and after 3 and 6 months) will be collected using electronic diaries and questionnaires included in the app.

The primary outcome measure will be the mean LBP or NP intensity during the first 3 months of intervention based on daily pain intensity measurements on a NRS (0 = no pain, 10 = worst possible pain). The secondary outcome parameters will include the mean pain intensity during the first 6 months after randomization based on daily measurements, the mean pain intensity measured weekly as the average pain intensity of the previous 7 days over 3 and 6 months, pain acceptance, ‘LBP- and NP-related’ stress, sick leave days, pain medication intake, adherence, suspected adverse reaction, and serious adverse events.

**Discussion:**

The designed studies reflect a usual self-care setting and will provide evidence on a pragmatic self-care intervention that is easy to combine with care provided by medical professionals.

**Trial registration:**

ClinicalTrials.gov identifier Relaxback NCT02019498, Relaxneck NCT02019134 registered on 18 December 2013.

## Background

Low back pain (LBP) and neck pain (NP) are highly prevalent conditions in industrialized countries with an estimated lifetime prevalence of 84% [1] and 30 to 70%, respectively [2, 3]. Of 281 conditions investigated in the Global Disease Study 2010, LBP ranked first and NP ranked fourth on a measure of years lived with disability in Western Europe [4, 5]. The global point prevalence of LBP was 9.4% (95% CI 9.0 to 9.8) [6] and that of NP was 4.9% (95% CI 4.6 to 5.3) [7]. In a representative survey of the German population from 2009, 20.7% of the respondents reported to have had LBP for at least 3 months in the previous year [8]. Work absence, disability and medical costs related to LBP and NP generate a high individual and societal burden [4, 9, 10]. Individuals suffer from a decrease in their quality of life and societal ramifications include absenteeism and early retirement [10, 11]. In Germany, the annual costs (direct and indirect) of back pain have been estimated at 16.4 to 50 billion Euro (approximately 2.2% of the gross domestic product in 2006) [12]. Although the majority of patients experience pain relief within 3 months, approximately 5 to 20% of individuals with LBP [13] and NP [14, 15] will develop sub-acute and chronic LBP. Numerous LBP and NP treatments exist, although available evidence suggests no more than moderate effects from most of the available treatments [16, 17]. Pain experts agree that most pain is best treated using a combination of medication with a self-management, complementary, non-drug therapy [18]. Therefore, in the last decade, multimodal treatment strategies have been established by national and international guidelines combining education, physiotherapy, medication, self-care and behavioral therapies [17, 19–23]. In the German national guidelines on LBP, paracetamol, NSAIDs and opioid analgesics (not longer than 3 months) are recommended as drug therapy. Physical activity, relaxation, ergotherapy, manipulation/mobilization, education, and behavioral therapies are recommended as non-drug therapies for chronic LBP [19]. Chronic NP should be treated with physiotherapy, and if necessary, in combination with manual therapy, post-isometric relaxation and muscle strengthening, and intramuscular injection of lidocaine. Other therapies based on patient preferences could be considered but cannot be recommended based on strong evidence [17]. The integration of active self-care therapies, such as ‘mind-body therapies’, for chronic pain treatment is supported by evidence [24]. Additionally, self-care interventions are highly attractive because they could reduce expenses for health care systems, are relatively safe, and might have health benefits beyond the effects on pain [24–27]. ‘Mind-body therapies’ including relaxation, meditation and guided imagery are easily applicable as self-care interventions and are used as adjuvant therapies for the treatment of chronic pain [28, 29]. One aim of several mind-body therapies, including relaxation techniques and meditation, is to reduce chronic stress and enhance well-being through the elicitation of the ‘relaxation response (RR)’ the opposite of the body’s stress response to perceived threats [30]. The RR is induced when a person focuses on a word, sound, phrase, repetitive prayer, or movement, and disregards everyday thought [31]. The relaxation response is defined as a physical state characterized by decreased arousal of the sympathetic nervous system [32] and is the opposite of the stress or ‘fight or flight’ response [30, 32]. Progressive muscle relaxation (PMR) has been shown to be an effective treatment for reducing chronic non-specific NP [33] and in Germany, PMR is recommended by the national disease management guidelines for LBP [19] and by the ‘guideline NP’ of the German Society of General Practice and Family Medicine [17]. ‘Mindfulness-based’ therapies have been shown to be effective based on clinical studies on the treatment of chronic pain [34], and a Cochrane review on patients with chronic LBP suggested that therapy using PMR or electromyographic (EMG) biofeedback is more effective than control treatments for pain relief and improving short-term functional status; however, this evidence was of low quality [35]. There has been encouraging evidence from a systematic review that showed that guided imagery can reduce musculoskeletal pain [36] and limited evidence that ‘mindfulness-based’ stress reduction improves pain acceptance [37]. Autogenic training (AT) is a commonly used self-help relaxation technique that is easily applicable in daily life [38]. Most of the mind-body therapies train patients in a group setting, but alternative delivery methods such as audio guidance from a smartphone may be more pragmatic in a usual care setting. Smartphones are increasingly common in the population. In Germany, it was estimated in February 2014 that 40 million people owned a smartphone [39], which is approximately 49.5% of the German population [40]. Coinciding with the popularity and wide utilization of smartphones, the number of available smartphone applications (apps) has increased rapidly [41], and apps are currently used to support people with various health problems. In a search conducted in July 2012, in the official Android, BlackBerry and iPhone Smartphone app platform stores in the United States, 220 pain apps were identified. Chronic non-specific pain was the focus of more than half (55.5%) of the apps followed by back pain and/or NP (25.9%) with the purpose of the apps being pain education (24.1%), pain self-management (62.3%) and both education and pain management (13.6%). Health care professionals were only involved in the development of a small number of these apps (35%) [42]. In a further search conducted between June and August 2010 in the official stores of the five major operating systems (iOS, Android, Blackberry OS, Nokia/Symbian and Windows Mobile) for available apps against pain, headache and migraine were the most commonly targeted conditions, followed by back pain. The reported purpose of the apps was mostly pain relief or educational information about pain. Apps that target pain often include an audio relaxation component. Regrettably, there is limited available information on the effectiveness of those apps as self-care interventions [41]. Furthermore, to date, the effectiveness of additional relaxation on chronic LBP or NP in a usual care setting is unclear. The aim of these two pragmatic randomized studies is to evaluate whether additional app-based delivered relaxation is more effective in the reduction of chronic LBP or NP than usual care alone.

## Methods/Design

### Design

Each study is a two-armed, randomized, parallel group, single center pragmatic trial investigating the effectiveness of additional relaxation exercise for patients with chronic LBP (Relaxback) and NP (Relaxneck) compared to usual care alone. The intervention duration is 6 months, with the primary outcome summarizing the effect in the first 3 months.

An app has been developed for collecting outcome data and to provide the relaxation intervention in the form of audio content to the participants of the intervention group.

As an essential part of comparative effectiveness research [43], stakeholders were included in the planning of the study. In July 2013, one stakeholder meeting included patients with NP (n = 3) and LBP (n = 4), psychologists (n = 2) and clinical researchers (n = 2). Stakeholder involvement resulted in the following resolutions:

Duration of the intervention was shortened from 20 to 15 minutes dailyParticipants can individually determine the time at which they will receive their push notificationsDiary content was determined (questions about the intensity of the pain, intensity of ‘LBP-/NP-related’ stress, adherence, and amount of pain medication intake)The German translation (Imaginationstraining) of guided imagery was determined.

### Participants

Potential participants will be informed with brochures and posters at universities, colleges, gyms, and doctors’ offices. The studies will include patients aged 18 to 65 years with chronic LBP or NP (≥12 weeks) and a mean pain score of ≥ 4 on a numeric rating scale (NRS) in the previous week. In order to be included in the studies, the patients have to be willing to be randomized and provide written and oral informed consent; furthermore, patients are required to follow study interventions according to the protocol, to complete the baseline questionnaire in paper form as well as electronic questionnaires and diaries provided by a smartphone application. Additionally, having a smartphone (iPhone or Android) is required. Participants must identify LBP or NP as their primary complaint to participate in the Relaxback or Relaxneck study, respectively.

Participants are excluded in case of their LBP/NP being caused by a known malignant disease, trauma, the presence of a known rheumatic disorder, a history or planned surgery of the spinal column of the low back/neck in the next 6 months, known neurological symptoms: for example, radicular symptoms because of a prolapsed disc, regular intake of analgesics (> once per week) because of additional disease, intake of centrally-acting analgesics, or a history of severe acute or chronic disorders that do not allow participation in the therapy. Further exclusion criteria include known alcohol or substance abuse, insufficient German language skills, current application for a pension claim, participation in another clinical trial during the 6 months before the study and parallel to the study or applying regular relaxation techniques, mindfulness meditation or any other ‘mindfulness-based’ therapy 6 weeks before the study or planned in the next 6 months.

### Randomization

For both studies, if a participant meets all inclusion and none of the exclusion criteria, they will be randomized to either the control (usual care only) or the intervention (usual care plus relaxation) group using blocked randomization with variable block lengths and an allocation ratio of 1:1, that is 110:110 participants for each study. The randomization sequence will be generated by a data manager, who will not be involved in the analysis of the data or the enrollment of the patients; SAS (version 9.3, SAS Inc., Cary, NC, USA) will be used for this process. The randomization list will be included in a safe Microsoft Access (Redmond, WA, USA) database to ensure that it is not accessible during the randomization process of individual participants and that screened patients are strictly consecutively enrolled. The randomization process will be conducted by the study office at the Institute for Social Medicine, Epidemiology, and Health Economics. To ensure allocation concealment upon inclusion into the study, the staff will enter participants into the database and will receive the intervention or control group allocations.

### The app

The app includes relaxation audio files, notification features, diaries, and questionnaire options. The app was developed for smartphones running the iOS or Android operating systems. The app concept was approved by the data protection officer of the Charité - Universitätsmedizin Berlin.

### Relaxation intervention

To induce a relaxation response, 3 exercises (AT, mindfulness meditation and guided imagery) with a length of 15 minutes each will be made available in 2 versions (female and male voice). They will be accompanied by a short instructional text. Relaxation exercises can be applied in different positions (sitting, walking and lying), which can be chosen by the participants according to their needs. The relaxation exercise should be applied daily or at least 5 days per week for 6 months.

AT was developed by the German psychiatrist Johannes Schultz in 1932. The AT audio has a focus on the physical sensation of the breath or heartbeat and visualizes the body as warm, heavy and/or relaxed [44]. The AT teaches participants to react to six verbal commands such as ‘my arms are very heavy’, ‘my heart beats regularly and calm’ and ‘my belly is warm’ to make the body feel relaxed.

Mindfulness is a practice rooted in *Vipassana* (translation: insight) meditation, which has Buddhist roots. It is defined as ‘paying attention in a particular way: on purpose, in the present moment and in a nonjudgmental way’ [45]. The mindfulness meditation focuses on the breath and uses the breath as an anchor when the mind starts to wander. This concept is also used in Mindfulness-Based Stress Reduction developed by Kabat-Zinn [45–47].

In guided imagery, the mind is directed to intentionally create images to produce positive changes [48]. The audio guides participants to visualize/conjure a place that is associated with positive feelings such as safety, security and well-being. The guided imagery audio is accompanied by soft background music and directs the visualization and imagination to a pleasant and peaceful place that has meaning for the participant to replace negative or stressful feelings [49].

### Control group

Patients in the control group continue using usual care defined as all medical and non-medical treatments; however, relaxation techniques, mindfulness meditation or any other mindfulness-based training are not permitted.

### Outcome measurement

The primary outcome measure will be the mean LBP or NP intensity during the first 3 months of intervention based on daily pain intensity measurements on a NRS (0 = no pain, 10 = worst possible pain) [50].

The secondary outcome parameters include the following: the mean pain intensity during the first 6 months after randomization based on daily measurements; the mean pain intensity (NRS) measured weekly as the average pain intensity of the previous 7 days over 3 and 6 months; pain acceptance (German version of Chronic Pain Acceptance Questionnaire [51]); ‘LBP-/NP-related stress’; sick leave days; and pain medication intake. Additionally, we will collect data about expectations, adherence, self-reported general changes in LBP/NP, suspected adverse reactions and serious adverse events. The outcome measures including the time points are listed in Table 1.

**Table 1 Tab1:** **Data collection: except for the baseline data, outcomes are assessed throughout the 6-month period**

	Baseline	Daily ^d^	Weekly ^d^	After third month ^d^	After sixth month ^d^
Socio-demographics (age, migration background, education)	x				
Pain intensity (NRS)		x			
Mean pain intensity in the last 7 days (NRS)	x		x		
Mean perceived ‘LBP-/NP-related’ stress intensity in the last 7 days (NRS)	x		x		
Pain acceptance	x			x	x
Sick leave days	x			x	x
Intake of medication against LBP/NP	x		x		
Suspected adverse reaction^a^				x	x
Serious adverse events				x	x
Application of other therapies	x			x	x
Expectation	x				
Adherence^a^		x^b^	x^c^		
Self-perceived improvement				x^a^	x^a^

^a^Only in the intervention group.

^b^Assessed by tracking.

^c^Assessed by the diary (for relaxation without audio use).

^d^Provided by the app.

Abbreviations: LBP, low back pain; NP, neck pain; NRS, numeric rating scale.

### Data collection

Baseline information will be collected using paper and pencil, and all follow-up data will be collected using the study app.

The study app features electronic daily and weekly diaries in which study participants will log daily data regarding their LBP/NP intensity and weekly data on medication intake, average pain intensity over the previous 7 days based on a NRS (‘How strong was your mean pain intensity in the last 7 days?’), and ‘LBP-/NP-related stress’. Daily and weekly data will be collected throughout the 6-month period. Furthermore, the apps include questionnaires that appear after the end of the third and sixth months.

### Assessment of adherence

Adherence will be assessed by 1) tracking of the running time of the relaxation audios (start and end times, and the type of relaxation) and 2) by asking the participants how much time they spent doing the relaxation exercises without using the app.

### Assessment of safety

Adverse events and suspected adverse reactions (only in the intervention group) are assessed after the third and sixth months using the questionnaire provided by the app.

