### Sample size

In the literature, an effect size of 0.62 has been described for mind-body therapies compared to no intervention in a group setting [29]. We assume a smaller effect size of 0.4 (Cohen’s d, baseline adjusted) for individual self-care relaxation exercise compared to usual care alone because individuals might be less focused and consequently less adherent in a self-care setting. To obtain a power of 80% using a 2-sided *t*-test with significance level of 0.05, 100 participants for each treatment group are needed (a total of 200 participants). We will include 110 participants per group (220 in total for each study) to compensate for dropouts.

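### The safety text and Table 1 disagree on which adverse events are collected; under Table 1, non-serious events have no control-arm counterpart.

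*Protocol article*

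**What the plan says.** The article mentions safety data in four places.

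- **Assessment of safety:** "Adverse events and suspected adverse reactions (only in the intervention group) are assessed after the third and sixth months", by means of the app questionnaire. Serious events are not named separately.
- **Table 1:** one row is "Suspected adverse reaction^a", where the footnote reads "Only in the intervention group". Another row is "Serious adverse events", without that footnote. Both are scheduled at months 3 and 6. There is no row for adverse events in general.
- **Outcome measurement:** the safety data to be collected are "suspected adverse reactions and serious adverse events", mentioned after the secondary outcomes as additional data.
- **Abstract, Methods/design:** the list of secondary outcomes ends with "adherence, suspected adverse reaction, and serious adverse events".

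The Data collection section adds that "all follow-up data will be collected using the study app".

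**The concern.** The safety section names a category, adverse events, that the other three places do not have, and it leaves out the category they do have, serious adverse events. Its parenthesis stands after two nouns, and the sentence alone does not show whether it limits one or both. Someone building or auditing the control-arm questionnaire from this article could not say whether controls are asked about non-serious events.

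The answer affects what can be concluded. If controls are not asked, the only non-serious harms item is the suspected reaction, which has two weaknesses:

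- It has no control value. Symptoms that people with chronic back or neck pain would report anyway cannot be separated from those the exercises cause.
- It counts an event only if the participant attributes it to the exercises, and the participant knows the allocation. The Discussion itself names lack of blinding as the main limitation and links it to bias in patient-reported outcomes.

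The Background gives relative safety as one attraction of self-care. A low count of suspected reactions could later be cited in support of that, although a one-arm, attribution-based count cannot show it.

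**Working it through.** The article gives no figure for safety, so the check is mainly a comparison of text.

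**Step 1. Item by item**

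| Item | Assessment of safety | Table 1 | Outcome measurement | Abstract |
|---|---|---|---|---|
| Adverse events, general | named; arm unclear | no row | not listed | not listed |
| Serious adverse events | not named | months 3 and 6, no arm restriction | listed | listed |
| Suspected adverse reactions | intervention group only | intervention group only | listed, arm not stated | listed, arm not stated |

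The only item on which the safety section and Table 1 agree is the suspected reaction.

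**Step 2. Possible readings of the safety sentence**

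- *A. Adverse events is loose wording for serious adverse events, and the parenthesis limits only suspected reactions.* This matches Table 1. Serious events are two-armed; non-serious events are one-armed and attribution-based.
- *B. Adverse events means all adverse events, and the parenthesis limits only suspected reactions.* Both arms are asked and a full comparison is possible. Table 1, Outcome measurement and the abstract then omit an item that is collected.
- *C. The parenthesis limits both nouns.* Controls are asked about no adverse events. If that includes serious ones, it contradicts the unrestricted row in Table 1.

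The parenthesis directly follows the second noun, and Table 1 marks only that row, so A or B is more natural than C. Nothing in the article decides between A and B, and they differ precisely on non-serious events in controls.

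**Step 3. What Table 1 allows for serious events**

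The only size calculation in the article concerns pain: "We assume a smaller effect size of 0.4 (Cohen’s d, baseline adjusted"). It reproduces: n = 2(1.960 + 0.842)²/0.4² = 98.1, so 99 per group by the normal formula, and 99.08, so 100, by the t-test, against 100 stated. It does not bear on safety.

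With 110 per arm, serious events can be compared, but imprecisely. The article gives no risks, so the following are assumptions:

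power = Φ{ [|p₂ − p₁| − 1.96·√(2p̄(1 − p̄)/n)] / √([p₁(1 − p₁) + p₂(1 − p₂)]/n) }

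- 2% vs 5%: (0.030 − 1.96 × 0.0248)/0.0247 = −0.75, power 23%.
- 2% vs 10%: (0.080 − 1.96 × 0.0320)/0.0316 = 0.55, power 71%.
- By the same formula, 5% vs 10% gives 29%, 5% vs 15% gives 70% and 5% vs 20% gives 93%.

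**Step 4. What a two-arm item would add for non-serious events**

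The 95% interval for a difference in proportions is widest when both are 50%. Its half-width is then 1.96·√(2 × 0.25/110) = 0.13. With 100 answering per arm it is 1.96·√(0.5/100) = 0.14. So, whatever the true rates, the half-width is at most about 13 to 14 percentage points per trial. Under reading A no such interval exists.

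**The case against.** **The stronger reading.** A reader might infer that all adverse events are collected in the intervention arm only and that the trials cannot compare harms. The documents do not support this. It needs reading C, the least natural one, and it passes over the Table 1 row for serious adverse events, which has no arm restriction. Serious harms can be compared.

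**The item may already be there.** Under reading B, controls are already asked about adverse events, and only Table 1 and the outcome lists need correcting. That is possible and cannot be excluded. It is also why the passages need reconciling: three of the four places show no such item.

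**One-arm suspected reactions are legitimate.** A suspected reaction is an event put down to the intervention, and controls receive none, so the restriction is no error in itself. Nor does the abstract's list promise a between-arm test: it also includes adherence, which Table 1 marks as intervention-only, and Outcome measurement places both outside the secondary outcomes. This stands. The weakness is that Table 1 has no attribution-free, two-arm item beside it.

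**App-only collection.** A reader might add that people who leave the app because of a bad experience are never asked. The article does route all follow-up data through the app, and safety is asked only at months 3 and 6. But nothing in it links stopping to harm, and contact after withdrawal and serious-event reporting are matters that a condensed article leaves to the full protocol. This is not part of the finding.

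**Burden.** The Discussion describes a deliberate effort to keep app questions few. That argues against more frequent safety questions, but hardly against one item in a questionnaire that already exists.

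**Conclusion.** The point holds as an inconsistency with a consequence. The article does not settle whether controls are asked about non-serious adverse events. If Table 1 is followed, the trials can compare serious events, with the limited precision shown above. For non-serious events they have an unblinded, attribution-based count in one arm, with no background rate and no randomised contrast.

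The size is structural: under Table 1, none of the non-serious harms items is two-armed. No figure for the number of events missed is offered, because the article gives no event rates. The direction of any error is also unknown, since attribution can both drop events and add coincidental ones.

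The conclusion assumes that Table 1 reflects what the app asks. If the app already puts a general adverse-event question to both arms, what remains is a documentation error. The primary pain analysis is unaffected either way.

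**What to change.** 1. Check what the live app asks control participants at months 3 and 6, then make Assessment of safety, Table 1, Outcome measurement and the abstract's list agree. State for each safety item which arm is asked and when.
2. Unless it is already asked, add one attribution-free adverse-event question, with a serious yes/no, for both arms in the existing month 3 and month 6 questionnaires. Give it its own row in Table 1.
3. Keep the suspected-reaction question as an intervention-only add-on and report it descriptively.
4. Compare the proportion with at least one event between arms as an exploratory analysis, consistent with the status of all analyses other than the primary one.

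**Cost.** One extra questionnaire item, an update to the iOS and Android apps, and an ethics notification for each trial. Recruitment began in March 2014, so the earliest participants reached month 6 around September 2014, before the article appeared in December. Participants already past a questionnaire would lack the item. The item should therefore go live in both arms at the same time, and the comparison should be limited by randomisation date to participants whose questionnaire fell due afterwards. That keeps it a randomised comparison in a smaller sample, with intervals wider than the 13 to 14 points given above.
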